***Figure 4: MUAC measuring tape.***

The MUAC is the circumference of the left upper arm that is measured at the mid-point between the tips of the shoulder and elbow. The participant’s left arm will be bent then the researcher will find and mark the mid-point between the two marks. There arm will be hanging straight down, and a MUAC tape will be wrapped around the arm at the midpoint mark. The MUAC will be measured to the nearest 1m (**see Appendix B**) for recording.

1. ***Dietary intake and patterns***

A one day 24-hour recall will be used to collect detailed information about all foods and beverages consumed using the multiple pass method (Steinfeldt *et al*., 2013). Foods will have been consumed in the past 24 hours, most commonly, from midnight to midnight the previous day (**see Appendix C)**. Six daily intervals will be included, namely: breakfast (period up to 09h00), In-between snack (between 09h00 and 12h00), lunch (12h00 to 14h00), In-between snack (14h00 to 18h00), dinner (18h00 to 20h00), and after dinner (after 20h00). Guardian/parents will provide this information. A FFQ will be used to establish food consumption patterns including the *Cucurbita moschata* seeds. A selected pictorial FFQ will be designed for the children to establish if they know and consume the seeds (**see Appendix D**). Preschool menu will also be evaluated at this stage using the 24 hr recall form for recording at least once a week during the implementation of the intervention.

1. ***Biochemical measurements***

Zinc status will be determined by serum zinc concentrations and iron status via haemoglobin, serum ferritin, transferrin receptor and C- reactive protein (CRP) among pre-school children using flame atomic absorption spectrophotometer. The anthropometric status of the preschool children will be assessed by measuring weight and height to calculate the body mass index (BMI).

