***Dietary patterns***

The 24-hour recall will be analysed using the 11-food item to determine dietary diversity score. The FFQ will be analysed using SPSS version 23 for frequencies as daily, weekly, monthly, seasonal or never. Consumption of indigenous foods will be determined using frequencies. Food finder (MRC) will also be used to analyse the nutrient intakes.

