**3.11 Dissemination of the information**

The results of this study will be reported using ta mixed dissertation format. Manuscripts for consideration in peer-reviewed journals will be drafted alongside during the finalisation of the dissertation. The proposed chapters will be:

Chapter one: Introduction

Chapter two: Literature review

Chapter three: Methodology

Chapter four: Development of *Cucurbita moschata* seeds recipes and nutrition education lesson on the importance of *Cucurbita moschata* using music.

Chapter five: Socio-economic and environmental parameters, nutritional status of children at baseline and six months after the intervention.

Chapter six: Consumption patterns of *Cucurbita moschata* (butternut) seeds, and their contribution to nutrient intake.

Chapter seven: The efficacy of the consumption of *Cucurbita moschata* seeds between the intervention and control groups, according to changes in zinc and iron status from baseline to post intervention (six months).

Chapter eight: Conclusions and recommendations

At least four articles are envisaged, two national and one international conferences presentations. A technical report will be prepared for sharing with the relevant institutions or government authority like the local and district municipalities, National or provincial Department of Social development, Department of Health, Department of Agriculture, Forestry and Fisheries and Department of Basic Education.

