**APPENDIX C: 24-hour recall**

| **Section: Dietary Patterns and Intakes of children** |
| --- |

**Please describe the foods (meals and snacks) that you ate yesterday during the day and night, whether at home or outside the home. Start with the first food eaten in the morning**

*Write down all food and drinks mentioned by the respondent. When the respondent has finished probe for meals and snacks not mentioned*

| **Meal** | **Time of meal** | **Food item description** |
| --- | --- | --- |
| **Breakfast** |  |  |
| **Snack** |  |  |
| **Lunch** |  |  |
| **Snack** |  |  |
| **Dinner** |  |  |
| **Snack** |  |  |

**[Household level: consider foods eaten by the child, and exclude foods purchased and eaten outside of the home or at the preschool]**

*When the respondent recall is complete, fill in the food groups based on the information recorded above. For any food groups not mentioned, ask the respondent if a food item from this group was consumed.*

| Question  number | Food group | Examples | Yes = 1  No = 0 |
| --- | --- | --- | --- |
|  | CEREALS | corn/maize, rice, wheat, sorghum, millet or any other grains or foods made from these (e.g. bread, noodles, porridge or other grain products) + *insert local foods e.g.* *ugali, nshima, porridge or pastes or other locally* *available grains* |  |
|  | VITAMIN A RICH VEGETABLES AND TUBERS | pumpkin, carrots, squash, or sweet potatoes that are orange inside + *other locally available vitamin-A rich* *vegetables (e.g. red sweet pepper)* |  |
|  | WHITE TUBERS AND ROOTS | white potatoes, white yams, white cassava, or other foods made from roots |  |
|  | DARK GREEN LEAFY VEGETABLES | dark green/leafy vegetables, including wild ones + *locally available vitamin-A rich leaves such as amaranth, cassava leaves, kale, spinach etc.* |  |
|  | OTHER VEGETABLES | other vegetables (e.g. tomato, onion, eggplant),  including wild vegetables |  |
|  | VITAMIN A RICH FRUITS | ripe mangoes, cantaloupe, apricots (fresh or dried), ripe papaya, dried peaches + *other locally available vitamin* *A-rich fruits* |  |
|  | OTHER FRUITS | other fruits, including wild fruits |  |
|  | ORGAN MEAT (IRON RICH) | liver, kidney, heart or other organ meats or blood-based foods |  |
|  | FLESH MEATS | beef, pork, lamb, goat, rabbit, wild game, chicken, duck, or other birds |  |
|  | EGGS | chicken, duck, guinea hen or any other egg |  |
|  | FISH | fresh or dried fish or shellfish |  |

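### Appendix C's note excluding preschool food contradicts the form's own opening prompt and section 3.6.2.5, so the child's diversity score and 24-hour intake may omit preschool meals

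*Protocol*

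**What the plan says.** Section 3.6.2.5 (Dietary intake and patterns) states the purpose of the recall: "A one day 24-hour recall will be used to collect detailed information about all foods and beverages consumed using the multiple pass method". It divides the day into six intervals, including a mid-morning snack and lunch, and names parents or guardians as respondents.

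Appendix C is the form used. It opens by asking for the foods "that you ate yesterday during the day and night, whether at home or outside the home" and tells the interviewer to write down everything mentioned. Below the meal grid, a bracketed note labelled as household level says to consider foods eaten by the child and to "exclude foods purchased and eaten outside of the home or at the preschool". The next instruction is to "fill in the food groups based on the information recorded above".

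On use of the data, the Dietary patterns paragraph of the baseline analysis says: "The 24-hour recall will be analysed using the 11-food item to determine dietary diversity score". Table 3.5 lists nutrient intake from the 24-hour recall and plans regressions with dietary intake as a dependent variable. Section 3.6.4.4 repeats the baseline procedures after the feeding period.

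On preschool food, section 3.6.2.5 adds: "Preschool menu will also be evaluated at this stage using the 24 hr recall form". This is to be done at least weekly during the intervention.

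**The concern.** The participants attend preschool, and the section on the intervention shows that lunch is taken there. A rule that removes preschool food therefore removes a main meal from the recorded day. The measures exposed are the dietary diversity score, 24-hour nutrient intake and the Table 3.5 analyses that use dietary intake. Better eating patterns and higher fruit and vegetable consumption are expected outcomes in section 2.5, so these measures carry some weight in the report.

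There are two possible harms. If every fieldworker follows the note, the measures describe home food while being reported as the child's diet. If some follow the note and others follow the opening prompt, the recalls mix two definitions, and nothing on the form shows which was used. Neither can be repaired in analysis, because a meal that was never written down cannot be recovered.

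**Working it through.** The documents state no figure to reproduce, so the check compares the text and then sets out what the note would remove.

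**1. The three instructions**

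| Place | Food eaten at the preschool |
|---|---|
| Section 3.6.2.5 | Included (all food and drink) |
| Appendix C, opening prompt | Included (home or outside) |
| Appendix C, bracketed note | Excluded |

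The household-level label does not separate the third line from the other two. The note itself speaks of food eaten by the child and names the preschool. The form gives no other scoring rule for the child; the individual-level and household-level lines at its end are only yes/no questions about eating outside the home.

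**2. What following the note removes**

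Let H be the food groups eaten at home, and O those eaten at the preschool or elsewhere, on the recalled day.

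- Diversity score with all food: the number of groups in H or O.
- Diversity score under the note: the number of groups in H.
- Loss: the number of groups in O that are not in H. It is zero if home meals already cover those groups, and one point for each group eaten only away from home.
- Nutrient intake loses the whole amount eaten away from home, with no such overlap.

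The documents place lunch at the preschool, so at least 1 of the 6 intervals is affected on a preschool day. If children also take the 09h00 to 12h00 snack there (an assumption, since attendance hours are not given), it is 2 of 6. A recall taken on a Monday covers Sunday and loses no preschool food.

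**3. Effect on comparisons**

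Let f be the fraction of recalls taken under the note, and L the mean loss when it is followed. The mean error is f × L. If f and L are equal in both arms, the between-arm error is zero. If f differs by d and L is the same, the between-arm error is d × L. L may also differ by arm, because whole preschools are randomised and a menu belongs to the preschool. The documents fix neither f nor L.

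**4. Whether another record fills the gap**

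| Record | What it covers | Restores a child's recalled day? |
|---|---|---|
| Food diary (section 3.6.3.5, Appendix F) | Home food only | No |
| Preschool menu record (3.6.2.5) | Menu level, during the intervention | No; no rule joins it to a child's recall, and survey days are not covered |
| Plate waste (3.6.3.5, Appendix E) | Test food, ten sampled children each time | No |
| Consumption record (3.6.3.6) | Test food only | No |
| FFQ (Appendix D) | All places, frequencies | No; it gives habits, not one day's intake |

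**The case against.** The best defence is that the form is an incompletely adapted template. The exclusion carries a household-level label, the opening prompt asks for everything, and fieldworkers will be trained, with methods standardised during piloting. On that view, preschool food may well be recorded. This stands in part: the loss is possible, not certain. It does not remove the defect, because the note is worded for the child and comes directly before scoring, and no document tells the fieldworker to ignore it.

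It is also fair that the same form serves both arms and both surveys, so a uniformly applied note could partly cancel in comparisons. It would not cancel in the descriptive intakes and scores.

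Three stronger readings are tempting and are not supported:

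- **That the recall misses the trial food because of this note.** The child recall is planned before feeding and after it. A test serving could fall in the recalled day only if the post-trial survey overlapped feeding days, which the Protocol does not state. Timing is the main reason. The same applies to any claim that the note hides displacement of the normal lunch by the paste.
- **That the seeds' share of intake would be overstated by a known factor.** Section 3.11 has only a thesis chapter title on the seeds "and their contribution to nutrient intake". No passage defines the calculation, and none gives the preschool share that it would need.
- **That no child-level form covers food at the preschool.** The FFQ is not limited to home food, and Appendix E records the test food by child. What is missing is a child-level record of the whole day.

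**Conclusion.** The contradiction is real and rests on the text alone. If the note is followed, the diversity score and 24-hour intake omit preschool meals at both surveys; if it is followed unevenly, recalls are not comparable. The loss covers one of six intervals on a recalled preschool day, or two if the mid-morning snack is also eaten there. Its size in nutrients or food groups cannot be derived from the documents.

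Severity is moderate. Diet is a secondary measure here. The primary aim concerns zinc and iron status, which is measured in blood and does not depend on this form, so a reader should not infer that the main efficacy result is at risk.

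**What to change.** Delete the bracketed note in Appendix C and put one child-level rule in its place: record everything your child ate and drank yesterday, at home, at the preschool and elsewhere. Change the opening prompt to address the child in the same way, since a parent or guardian answers.

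Parents may not know what was eaten at the preschool. The fieldworker should therefore complete those intervals from a preschool-menu record, and section 3.6.2.5 should say so. That record is now planned only during the intervention, so extend it to the days recalled at the baseline and post-trial surveys.

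The cost is one reworded form before baseline and a small amount of extra menu recording, with no added visits. A menu record shows what was offered and not what each child ate, so some error in the preschool intervals will remain and should be acknowledged in the report.

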**APPENDIX: D**

**SELECTED FOOD FREQUENCY QUESTIONNAIRE**

|  |  | **Average use** | | | | | | | |
| --- | --- | --- | --- | --- | --- | --- | --- | --- | --- |
| **Code** | **Food items** | **<1 month** | **1-3**  **Month** | **1 week** | **2-4**  **week** | **5-6**  **week** | **1 day** | **2-3**  **day** | **4+**  **day** |
| **Starchy food** | | | | | | | | | |
| **50** | Stiff MM porridge |  |  |  |  |  |  |  |  |
| **51** | Soft MM porridge |  |  |  |  |  |  |  |  |
| **52** | Fermented Soft MM porridge |  |  |  |  |  |  |  |  |
| **53** | Fermented Stiff MM porridge |  |  |  |  |  |  |  |  |
| **54** | Fermented home-made soft porridge |  |  |  |  |  |  |  |  |
| **55** | Samp |  |  |  |  |  |  |  |  |
|  | Rice |  |  |  |  |  |  |  |  |
|  | Macaroni |  |  |  |  |  |  |  |  |
|  | Spaghetti |  |  |  |  |  |  |  |  |
|  | Cooked maize cob |  |  |  |  |  |  |  |  |
|  | Roasted maize cob |  |  |  |  |  |  |  |  |
|  | Oats porridge |  |  |  |  |  |  |  |  |
|  | Muesli |  |  |  |  |  |  |  |  |
|  | Cornflakes |  |  |  |  |  |  |  |  |
|  | All bran |  |  |  |  |  |  |  |  |
|  | Brown Bread |  |  |  |  |  |  |  |  |
|  | Whole wheat bread |  |  |  |  |  |  |  |  |
|  | White bread |  |  |  |  |  |  |  |  |
|  | Home-made bread |  |  |  |  |  |  |  |  |
|  | Dumpling |  |  |  |  |  |  |  |  |
|  | Fat-cakes |  |  |  |  |  |  |  |  |
|  | Scones |  |  |  |  |  |  |  |  |
|  | Cakes |  |  |  |  |  |  |  |  |
|  | Muffins |  |  |  |  |  |  |  |  |
|  | Biscuits |  |  |  |  |  |  |  |  |
| **Protein foods (Meat and meat product)** | | | | | | | | | |
|  | Chicken drumstick (F/S) |  |  |  |  |  |  |  |  |
|  | Chicken thigh (F/S) |  |  |  |  |  |  |  |  |
|  | Chicken breast (F/S) |  |  |  |  |  |  |  |  |
|  | Chicken wing (F/S) |  |  |  |  |  |  |  |  |
|  | Stewed chicken feet |  |  |  |  |  |  |  |  |
|  | Chicken heads |  |  |  |  |  |  |  |  |
|  | Chicken liver |  |  |  |  |  |  |  |  |
|  | Chicken gizzard |  |  |  |  |  |  |  |  |
|  | Chicken necks |  |  |  |  |  |  |  |  |
|  | Chicken giblets |  |  |  |  |  |  |  |  |
|  | Stewed chicken |  |  |  |  |  |  |  |  |
|  | Barbequed/grilled chicken |  |  |  |  |  |  |  |  |
|  | Braai or dusty chicken |  |  |  |  |  |  |  |  |
|  | Stewed Turkey |  |  |  |  |  |  |  |  |
|  | Beef stew |  |  |  |  |  |  |  |  |
|  | Braai beef |  |  |  |  |  |  |  |  |
|  | minced meat |  |  |  |  |  |  |  |  |
|  | Ox Tripe |  |  |  |  |  |  |  |  |
|  | Ox Liver |  |  |  |  |  |  |  |  |
|  | Ox tail |  |  |  |  |  |  |  |  |
|  | Canned beef |  |  |  |  |  |  |  |  |
|  | Lamb/mutton stew |  |  |  |  |  |  |  |  |
|  | Pork stew |  |  |  |  |  |  |  |  |
|  | Grilled pork |  |  |  |  |  |  |  |  |
|  | Goat stew |  |  |  |  |  |  |  |  |
|  | Polony |  |  |  |  |  |  |  |  |
|  | Russian |  |  |  |  |  |  |  |  |
|  | Vienna |  |  |  |  |  |  |  |  |
|  | Bacon |  |  |  |  |  |  |  |  |
|  | Wors |  |  |  |  |  |  |  |  |
|  | Canned Fish |  |  |  |  |  |  |  |  |
|  | Fried fish |  |  |  |  |  |  |  |  |
|  | Steamed/boiled fish |  |  |  |  |  |  |  |  |
|  | Crumbed fish |  |  |  |  |  |  |  |  |
|  | Dried smoked fish (bak fish) |  |  |  |  |  |  |  |  |
|  | Locust |  |  |  |  |  |  |  |  |
|  | Mopani worms/Matomani |  |  |  |  |  |  |  |  |
|  | Termites |  |  |  |  |  |  |  |  |
|  | Ntshwamakhura/Tintshwa |  |  |  |  |  |  |  |  |
|  | Jengelengende |  |  |  |  |  |  |  |  |
| **Milk and milk product** | | | | | | | | | |
|  | Fresh cow milk |  |  |  |  |  |  |  |  |
|  | Sour cow milk |  |  |  |  |  |  |  |  |
|  | Pasteurised full cream cow’s milk |  |  |  |  |  |  |  |  |
|  | Skimmed/ fat free milk |  |  |  |  |  |  |  |  |
|  | Low fat milk |  |  |  |  |  |  |  |  |
|  | Powdered cow milk (Nespray, Klim) |  |  |  |  |  |  |  |  |
|  | Condensed milk |  |  |  |  |  |  |  |  |
|  | Fresh full cream Yoghurt |  |  |  |  |  |  |  |  |
|  | Low fat, sweetened yoghurt |  |  |  |  |  |  |  |  |
|  | Drinking yoghurt (Yogi sip |  |  |  |  |  |  |  |  |
|  | Coffee creamer (cremora, ellis brown etc) |  |  |  |  |  |  |  |  |
|  | Ice-cream |  |  |  |  |  |  |  |  |
|  | Cheese (specify) |  |  |  |  |  |  |  |  |
|  | Boiled Eggs |  |  |  |  |  |  |  |  |
|  | Fried eggs |  |  |  |  |  |  |  |  |
|  | Scrambled eggs |  |  |  |  |  |  |  |  |
|  | Mayo |  |  |  |  |  |  |  |  |
|  | Inkomazi/Maas |  |  |  |  |  |  |  |  |
| **Legumes** | | | | | | | | | |
|  | Baked beans |  |  |  |  |  |  |  |  |
|  | Sugar beans |  |  |  |  |  |  |  |  |
|  | soypeas |  |  |  |  |  |  |  |  |
|  | Kidney beans |  |  |  |  |  |  |  |  |
|  | Chicken peas |  |  |  |  |  |  |  |  |
|  | Boiled Jugo beans |  |  |  |  |  |  |  |  |
|  | Boiled dried cowpeas |  |  |  |  |  |  |  |  |
|  | Boiled fresh cowpeas in pod |  |  |  |  |  |  |  |  |
|  | Stewed cowpeas |  |  |  |  |  |  |  |  |
|  | Butter beans |  |  |  |  |  |  |  |  |
|  | Red Lentils |  |  |  |  |  |  |  |  |
|  | Brown/black lentils |  |  |  |  |  |  |  |  |
|  | Soya beans |  |  |  |  |  |  |  |  |
|  | Boiled fresh groundnuts |  |  |  |  |  |  |  |  |
|  | Roasted groundnuts |  |  |  |  |  |  |  |  |
|  | Soya mince |  |  |  |  |  |  |  |  |
|  | Processed and packaged peanuts |  |  |  |  |  |  |  |  |
|  | Macadamia nuts |  |  |  |  |  |  |  |  |
|  | Pecan nuts |  |  |  |  |  |  |  |  |
|  | Marula nuts |  |  |  |  |  |  |  |  |
|  | Roasted butternuts seeds |  |  |  |  |  |  |  |  |
|  | Canned Peas |  |  |  |  |  |  |  |  |
|  | Frozen or Fresh cooked peas |  |  |  |  |  |  |  |  |
|  | Dried boiled peas |  |  |  |  |  |  |  |  |
|  | Mungbean (Ndodzi) |  |  |  |  |  |  |  |  |
| **Fruits** | | | | | | | | | |
|  | Apple |  |  |  |  |  |  |  |  |
|  | Banana |  |  |  |  |  |  |  |  |
|  | Orange |  |  |  |  |  |  |  |  |
|  | Avocado |  |  |  |  |  |  |  |  |
|  | Granadilla |  |  |  |  |  |  |  |  |
|  | Lemon |  |  |  |  |  |  |  |  |
|  | Litchi |  |  |  |  |  |  |  |  |
|  | plums |  |  |  |  |  |  |  |  |
|  | Pawpaw |  |  |  |  |  |  |  |  |
|  | Grapes |  |  |  |  |  |  |  |  |
|  | Guava |  |  |  |  |  |  |  |  |
|  | Mango |  |  |  |  |  |  |  |  |
|  | Naartjie |  |  |  |  |  |  |  |  |
|  | Peach |  |  |  |  |  |  |  |  |
|  | Pear |  |  |  |  |  |  |  |  |
|  | Pineapple |  |  |  |  |  |  |  |  |
|  | Sugar cane |  |  |  |  |  |  |  |  |
|  | Apricots |  |  |  |  |  |  |  |  |
|  | Watermelon |  |  |  |  |  |  |  |  |
|  | Mudoro |  |  |  |  |  |  |  |  |
|  | Titshuguru (Natal plum) |  |  |  |  |  |  |  |  |
|  | Titsengele (Sour plum) |  |  |  |  |  |  |  |  |
|  | Mapfilwa |  |  |  |  |  |  |  |  |
|  | Makwakwa (Baboon orange) |  |  |  |  |  |  |  |  |
|  | Masala |  |  |  |  |  |  |  |  |
|  | Baobab fruit |  |  |  |  |  |  |  |  |
|  | Fig |  |  |  |  |  |  |  |  |
|  | Tintoma |  |  |  |  |  |  |  |  |
|  | Nombela (African Litchie) |  |  |  |  |  |  |  |  |
|  | Marula fruit |  |  |  |  |  |  |  |  |
|  | Tinyiyi |  |  |  |  |  |  |  |  |
|  | Xirhomberhombe |  |  |  |  |  |  |  |  |
|  | Mobola plum(muvhula/ timbulwa) |  |  |  |  |  |  |  |  |
| **Vegetables** | | | | | | | | | |
|  | Cooked spinach |  |  |  |  |  |  |  |  |
|  | Stewed spinach (tomato, onion) |  |  |  |  |  |  |  |  |
|  | Stewed spinach (with potato) |  |  |  |  |  |  |  |  |
|  | Stewed spinach with nuts |  |  |  |  |  |  |  |  |
|  | Stewed spinach with milk/cream |  |  |  |  |  |  |  |  |
|  | Boiled Potato skin |  |  |  |  |  |  |  |  |
|  | Shallow fried potato |  |  |  |  |  |  |  |  |
|  | Baked potato |  |  |  |  |  |  |  |  |
|  | Mashed potato |  |  |  |  |  |  |  |  |
|  | Potato salad with mayonnaise |  |  |  |  |  |  |  |  |
|  | Boiled White-flesh sweet potato |  |  |  |  |  |  |  |  |
|  | Boiled Yellow-flesh sweet potato |  |  |  |  |  |  |  |  |
|  | Boiled Orange-flesh sweet potato |  |  |  |  |  |  |  |  |
|  | Boiled carrots |  |  |  |  |  |  |  |  |
|  | Stewed carrots |  |  |  |  |  |  |  |  |
|  | Raw carrot |  |  |  |  |  |  |  |  |
|  | Carrot salad |  |  |  |  |  |  |  |  |
|  | Boiled pumpkin leaves |  |  |  |  |  |  |  |  |
|  | Boiled Butternut |  |  |  |  |  |  |  |  |
|  | Butternut cooked with margarine and sugar |  |  |  |  |  |  |  |  |
|  | Boiled mushrooms |  |  |  |  |  |  |  |  |
|  | Stewed Baby marrow |  |  |  |  |  |  |  |  |
|  | Boiled Rhanga |  |  |  |  |  |  |  |  |
|  | Tomato gravy with onion |  |  |  |  |  |  |  |  |
|  | Raw Tomato with salt |  |  |  |  |  |  |  |  |
|  | Tomato salad |  |  |  |  |  |  |  |  |
|  | Beetroot salad |  |  |  |  |  |  |  |  |
|  | Canned/bottled beetroot |  |  |  |  |  |  |  |  |
|  | Stewed beetroot leaves |  |  |  |  |  |  |  |  |
|  | Boiled Cabbage |  |  |  |  |  |  |  |  |
|  | Fried cabbage |  |  |  |  |  |  |  |  |
|  | Stewed cabbage (onion, tomato or potato and oil) |  |  |  |  |  |  |  |  |
|  | Cabbage salad |  |  |  |  |  |  |  |  |
|  | Stewed Cowpea leaves with oil, tomato and onion. |  |  |  |  |  |  |  |  |
|  | Stewed Cowpea leaves with peanuts |  |  |  |  |  |  |  |  |
|  | Dried cowpea  leaves with oil, onion and tomato |  |  |  |  |  |  |  |  |
|  | Dried cowpea leaves with crushed peanuts or peanut butter |  |  |  |  |  |  |  |  |
|  | Stewed Pumpkin leaves with flower and baby marrow with groundnuts |  |  |  |  |  |  |  |  |
|  | Stewed Pumpkin leaves with crushed groundnuts |  |  |  |  |  |  |  |  |
|  | Stewed pumpkin leaves with tomato |  |  |  |  |  |  |  |  |
|  | Stewed dried Pumpkin leaves with flower and groundnut s |  |  |  |  |  |  |  |  |
|  | Stewed Muxiji with onion, tomato and salt |  |  |  |  |  |  |  |  |
|  | Stewed Muxiji with crushed groundnuts or peanut butter |  |  |  |  |  |  |  |  |
|  | Stewed Muxiji with Amaranthus and salt |  |  |  |  |  |  |  |  |
|  | Boiled Cleome gynandra with salt (Bangala) |  |  |  |  |  |  |  |  |
|  | Stewed Cleome with tomato, onion and oil |  |  |  |  |  |  |  |  |
|  | Stewed Cleome gynandra with tomato and onion |  |  |  |  |  |  |  |  |
|  | Boiled Cleome gynandra crushed groundnuts |  |  |  |  |  |  |  |  |
|  | Stewed Dried Cleome and crushed groundnuts |  |  |  |  |  |  |  |  |
|  | Boiled Amaranthus with salt (Vowa)) |  |  |  |  |  |  |  |  |
|  | Stewed Amaranthus with tomato, onion and oil |  |  |  |  |  |  |  |  |
|  | Stewed with Amaranthus with tomato and onion |  |  |  |  |  |  |  |  |
|  | Boiled Amaranthus with crushed groundnuts |  |  |  |  |  |  |  |  |
|  | Stewed Dried Amaranthus and crushed groundnuts |  |  |  |  |  |  |  |  |
|  | Boiled fresh Guxe (Jute plant) |  |  |  |  |  |  |  |  |
|  | Boiled dried Guxe, with *Mormodica balsamina* (Nkanka) |  |  |  |  |  |  |  |  |
|  | Boiled dried Guxe with tomato |  |  |  |  |  |  |  |  |
|  | Boiled Okra leaves |  |  |  |  |  |  |  |  |
|  | Boiled Okra leaves with tomato |  |  |  |  |  |  |  |  |
|  | Boiled okra leaves and fruit |  |  |  |  |  |  |  |  |
|  | Boiled okra fruit with tomatoes |  |  |  |  |  |  |  |  |
|  | Stewed Mormodica leaves with fruits, tomatoes and onions |  |  |  |  |  |  |  |  |
|  | Stewed Mormodica with crushed groundnuts |  |  |  |  |  |  |  |  |
|  | Boiled Chinese spinach |  |  |  |  |  |  |  |  |
|  | Stewed Chinese spinach with tomato, onion and oil |  |  |  |  |  |  |  |  |
|  | Stewed Chinese spinach with crushed groundnut |  |  |  |  |  |  |  |  |
|  | Green pepper |  |  |  |  |  |  |  |  |
|  | Red Pepper |  |  |  |  |  |  |  |  |
|  | Yellow pepper |  |  |  |  |  |  |  |  |
|  | Onion |  |  |  |  |  |  |  |  |
|  | Kale or MuRhodesia (Choumolia- green leafy veg |  |  |  |  |  |  |  |  |
|  | Fried Onion |  |  |  |  |  |  |  |  |
|  | Cucumber |  |  |  |  |  |  |  |  |
|  | Lettuce |  |  |  |  |  |  |  |  |
| **Beverages** | | | | | | | | | |
|  | Water |  |  |  |  |  |  |  |  |
|  | Tea |  |  |  |  |  |  |  |  |
|  | Rooibos |  |  |  |  |  |  |  |  |
|  | Coffee |  |  |  |  |  |  |  |  |
|  | Fruit Juice |  |  |  |  |  |  |  |  |
|  | Squashes (diluted e.g Oros) |  |  |  |  |  |  |  |  |
|  | Cold drinks |  |  |  |  |  |  |  |  |
|  | Fizzy drink |  |  |  |  |  |  |  |  |
|  | Dairy fruit mix |  |  |  |  |  |  |  |  |
|  | Homemade mahewu |  |  |  |  |  |  |  |  |
|  | Home-made Ginger drink (Gemmer) |  |  |  |  |  |  |  |  |
|  | Purchased mageu |  |  |  |  |  |  |  |  |
|  | Flavoured mageu |  |  |  |  |  |  |  |  |
|  |  |  |  |  |  |  |  |  |  |
|  |  |  |  |  |  |  |  |  |  |
|  |  |  |  |  |  |  |  |  |  |

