The most frequently consumed *Cucurbita* species in South Africa is *Cucurbita Moschata*. Studies have shown that the seeds of *Cucurbita* *spp* are consumed all over the world. However, at the domestic scale they are consumed raw, roasted or cooked (Aruah *et al*., 2011; Patel, 2013). Several studies have dealt with the benefits of consuming *Cucurbita Moschata* flesh and leaves (Yadav *et al*., 2010; [Kim](https://www.ncbi.nlm.nih.gov/pubmed/?term=Kim%20MY%5BAuthor%5D&cauthor=true&cauthor_uid=22413037) *et al*., 2012; Wang *et al*., 2012, Durante *et al*., 2014; Dias *et al*. 2015). Yet limited studies exist on the beneficial effects of consuming *Cucurbita moschata (CM)* seeds. The present study is, therefore, designed to evaluate effectiveness of *CM* (Butternut) seeds consumption in the management of iron and zinc deficiencies in preschool children, aged 3-5 years.

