**1.9 Problem statement**

It has been estimated that zinc deficiency affects about one-third of the world’s population, with a prevalence of 4% to 73% across sub regions in Sub Saharan Africa. This degree of inadequacy is shocking when the requirements of iron and zinc are lacking. Growth is impeded, immune function is depressed, hair is lost, and susceptibility to and severity of infections is increased. In addition, neurobehavioral abnormalities occur due to increased number of opiate receptors in the hypothalamus, in parallel with decreased beta-endorphin and increase metenkephalin (Mahan *et al*., 2012). Iron deficiency and iron deficiency anaemia are two of the most common nutritional deficiencies among children in the world (Monárrez-Espino *et al*., 2011; Mahan *et al*., 2012). The WHO estimates that iron deficiency anaemia affects quarter of the world population and is more prevalent in pre-school children, particularly Africa. Furthermore, the deficiency of these micronutrients is caused by consumption of staple foods and cereal crops that have low micronutrient bioavailability (Uchendu, 2011).

*Cucurbita moschata* (butternut) seeds are considered generally to be agro-industrial wastes and are discarded (Patel, 2013; Patela and Raufb, 2017). In many communities around the world, the seeds are consumed raw, roasted or cooked, but only at the domestic scale. In addition, many communities in South Africa use to consume the roasted *Cucurbita moschata* seeds with porridge. Consumption has been associated with poverty. Instead of being used as a food source, these are discarded or preserved for future use. *Cucurbita moschata* contains adequate levels of minerals such as iron, zinc, copper, calcium, potassium and phosphorus (Patel, 2013; Patela and Raufb, 2017). Despite the legislated fortification of staple foods in South Africa since 2003 (SANHANES-1, 2013), there is a general shortage of micronutrients in a large part of the diet of the population. Inadequate micronutrient intake also has been identified among segments of infant’s in South Africa due to improper practices of feeding children.

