Promotion of the consumption of the seeds and nutrition education will be done in the form of a song, which is known to be the best method for educating children under the age of five years. The training on the consumption of the seeds will involve the guardian/parents during participant’s recruitment because children at this age are still fully dependent for food on their caregivers/parents who thus influence their eating habits (Curtis *et al*., 2011). The focus of the training will be on the health benefits of consuming seeds of *Cucurbita* *spp.* The songs will be easily learned by preschool children and will become favourites because of their familiarity. Furthermore, the songs will build confidence in preschool children and even shy children are likely to participate as part of a group or whole class. The recorded lyrics during the Pilot will be used. The table below is a schematic representation of the feeding trial.

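### The food frequency questionnaire's only seed item is roasted butternut seeds, so seed consumption measured by it may miss raw, cooked or ground use

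*Protocol*

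**What the plan says.** Section 3.6.2.5 (Dietary intake and patterns) gives the FFQ the task of establishing food consumption patterns, with the *Cucurbita moschata* seeds expressly included. It adds: "A selected pictorial FFQ will be designed for the children to establish if they know and consume the seeds", and points to Appendix D. The FFQ is used at baseline (section 3.6.2.2) and again after the trial (section 3.6.4.2). Section 3.11 plans a dissertation chapter on consumption patterns of the seeds and their contribution to nutrient intake.

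In Appendix D the only row about seeds is "Roasted butternuts seeds", under Legumes. The other butternut rows are flesh dishes, such as "Butternut cooked with margarine and sugar".

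On how seeds are eaten, section 1.7 says that "at the domestic scale they are consumed raw, roasted or cooked", and section 1.9 repeats this: "the seeds are consumed raw, roasted or cooked, but only at the domestic scale". Section 2.6 says they can be a raw or roasted snack. For local practice, section 1.9 says that "many communities in South Africa use to consume the roasted" seeds, with porridge. The trial food (section 3.6.3, Intervention and data collection) is ground seed mixed with cooked flesh.

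**The concern.** The form names one preparation of the study food, while the protocol names several and serves yet another. A caregiver who reads the row as written would record no seed use for a child who eats seeds raw, cooked, or ground into a paste like the one served at preschool. The FFQ is the only instrument used at both surveys that has an item dedicated to the seeds, so the planned description of seed consumption rests largely on this row.

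Home use is foreseeable. Parents are trained about the seeds at recruitment ("The focus of the training will be on the health benefits of consuming seeds of" *Cucurbita* species), and the text does not limit that training to the experimental preschools. At stake are the accuracy of a descriptive result and one source of help in interpreting the trial comparison.

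**Working it through.** The protocol states no figure for seed use, so there is nothing to reproduce. The check is a comparison of the form with the text.

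**1. Forms of seed use against FFQ rows**

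| Form | Where the protocol mentions it | Row in Appendix D |
|---|---|---|
| Roasted | Sections 1.7, 1.9, 2.6 | Yes |
| Raw | Sections 1.7, 1.9, 2.6 | None |
| Cooked | Sections 1.7, 1.9 | None |
| Ground, in paste with flesh | Section 3.6.3 (trial food) | None |

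One row covers one of the three forms named in the background, and no row covers the form used in the trial.

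**2. Would a caregiver read the row broadly?** The form's own layout suggests not. It separates preparations of the same food: boiled, roasted and packaged groundnuts have three rows, cowpeas in the Legumes block have three, and pumpkin leaves have five. On such a form, the word roasted reads as a restriction.

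**3. What the other instruments add**

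- 24-hour recall (Appendix C): used at both surveys, with open-text entries and a probe for any food group not mentioned. It covers one day per survey, and its group tally pools seeds with legumes and nuts.
- Food diary (section 3.6.3.5, Appendix F): one day per week for six months, in open text, so any form of seed can be written down. It belongs to the intervention phase, so it gives no baseline, and it has no seed prompt.
- Plate waste form (Appendix E): records trial servings only, for ten randomly selected children each time (section 3.6.3.5).

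**4. Size.** Let q be the share of seed-eating children who eat seeds only in non-roasted form, and suppose that caregivers read the row literally. Then

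share of true users recorded = 1 − q.

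The documents give no value for q. For illustration only:

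- q = 0: 1 − 0 = 100% recorded
- q = 0.25: 1 − 0.25 = 75% recorded
- q = 0.5: 1 − 0.5 = 50% recorded

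**The case against.** The strongest reply is that the row fits local habit. The list of raw, roasted and cooked use describes practice around the world. The only South African practice reported is roasted seeds with porridge, and section 2.6 states a possibility, not a local observation. This stands, and it is why the FFQ can be said only to be liable to miss use, not shown to miss it. It does not remove the gap. The trial and its parent training may prompt new forms of use, notably home versions of the paste.

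A second reply is that the diary and recall accept any form of seed. That is correct, with the limits set out in the working.

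Four stronger inferences are tempting, and the documents do not support them:

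- **Contamination of the control arm is under-counted, so a null result could not be interpreted.** No section makes the FFQ the contamination measure, and the diary records home intake during the six months. Any dilution would come from control children eating seeds, not from the wording of the row. A fuller row would help interpretation but would not change the contrast.
- **The under-count can be quantified.** Any assumed level of control use or split between forms would have no source in the protocol.
- **The absence of an item on knowing the seeds is an error.** Section 3.6.2.5 assigns this to a pictorial FFQ that is still to be designed. Appendix D as shown is a text table, and figures are missing from the copy reviewed.
- **Naming butternut alone is a defect.** The trial food and the planned chapter concern *Cucurbita moschata*, which section 1.7 calls the most frequently consumed *Cucurbita* species in South Africa. Only the parents' training refers to the wider group.

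**Conclusion.** The point holds as a gap in questionnaire content. The FFQ is meant to establish consumption of the seeds, but its single seed item is limited to roasted seeds. FFQ-based seed consumption at baseline and six months may therefore miss raw, cooked or ground use, including home copies of the study paste. The recall and diary close the gap only partly.

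The size cannot be derived from the documents. It depends on the share of non-roasted use and on caregivers reading the row literally, and it is zero if all use is roasted. Serum zinc and the iron indices are not affected. What is affected is the descriptive result on seed consumption and the help it could give in reading the arm comparison. This is a minor point, worth correcting before baseline because baseline answers cannot be recovered later.

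**What to change.** Before baseline data collection:

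1. Replace the roasted-seed row in Appendix D with *butternut or pumpkin seeds, any form (raw, roasted, cooked, ground or in a dish)*. Separate rows by form are an alternative if the breakdown is wanted.
2. Instruct interviewers to count only servings eaten outside the trial. Otherwise, at six months, the broader row would pick up the preschool paste. Take trial servings from the consumption record described in section 3.6.3.6. Appendix E cannot supply them, because it is completed only for the ten children sampled each time.
3. Report any seed use outside the trial by arm at baseline and six months, read together with seed entries in the food diary.

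The cost is one or a few extra lines on an existing form, one interviewer instruction and one descriptive table.
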